### 2.4. Randomization, allocation concealment, and blinding

Eligible participants will be divided randomly into the intervention group (ACE group) or the control group (sham ACE group). The random numbers of allocation sequences will be generated using Statistical Analysis System (version 9.4) by a statistician. Later, the random numbers and groupings will be packaged in opaque and closed envelopes with sequence numbers. The researchers responsible for the participant’s enrolment will take the envelopes with the corresponding number according to the inclusion order, and write down the name, gender, and age of the included participant on the surface of the envelope. All the marked envelopes will be kept by another researcher, who is not involved in participant recruitment.

After the baseline assessment of personal conditions and pre-treatment outcome measurements, acupuncturists will be informed about the different treatments of the participants. The outcome assessors will be blinded to the treatments due to the groups of the participants recorded in the case record forms (CRFs) being replaced by “A” and “B” without details. Additionally, the assessors will also be blinded to recruitment and groupings. All in all, participants, outcome assessors, and statistician in the study will be blinded to the different treatments. Under certain conditions, unblinding will be permissible when participants undergo SAEs or other emergency situations. Once unblinded, participants will withdraw from the trial, and the reasons will be documented and reported by the researchers.

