#### 2.6.1. Intervention group

(1)**Acupoints:** According to the theory of TCM and previous clinical practice experience, this study will select the bilateral acupoints of Shenshu (BL23) and Dachangshu (BL25). The position and depth of acupoints for needle insertion are in accordance with the Name and Location of Acupoints (GB/T12346-2006), a standard of The People’s Republic of China. Details of selected acupoints are shown in Table 1 and Figure 2.(2)**Preparation of ACE:** The main instruments utilized in the ACE treatment operation include an embedding needle, combinating of needle tubing and liner core, and absorbable surgical chromic catgut (Yangzhou Longhu Medical Instrument Co., Ltd., Yangzhou City, Jiangsu Province, China), all of which are disposable sterile products. The embedding needle is shown in Figure 3. Participants will stay in the prone position during the operation process.(3)**Operation procedures:** Firstly, the skin of the target acupoint region will be exposed and sterilized with iodophor. After disinfecting hands and wearing sterile gloves, the acupuncturists will cut the absorbable surgical chromic catguts into 1 cm long pieces, and place the small catgut into the pinpoint of the embedding needle tubing, where the liner core will be moved up 1 cm. Then, acupuncturist will use the thumb and index fingers to fix the acupoint, while, with the other hand, inserting the needle perpendicularly to the skin surface of the acupoint at a depth of approximately 1 cm. Secondly, acupuncturists will apply lifting, inserting, and twisting techniques to stimulate special sensations, presenting soreness, such as numbness, swelling, or radiation, but no pain, which are described as *Deqi* in TCM theory. Thirdly, by pressing down the liner core of the embedding needle, the catgut in the needle tubing will be embedded in the muscle layer. Finally, both the liner core and needle tubing will be pulled out of the acupoint, and the post-treatment acupoint will be covered by a cotton ball with tape for 24 h.

**TABLE 1 T1:** Locations of acupoints in the study.

	Acupoints	
	BL23 Bladder meridian	BL25 Bladder meridian
Needle insertion	On the lumbar region, on the same level of the second subspinous of the lumbar vertebra, and 1.5 cun lateral to the posterior midline.	On the lumbar region, on the same level of the fourth subspinous of the lumbar vertebra, and 1.5 cun lateral to the posterior midline.

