#### 2.6.2. Control group

In the sham ACE group, the embedding needle and acupoints are the same as those of the intervention group, but no catgut will be placed into the needle tubing before being inserted into the acupoints, so that no catgut will be left under the tissue after the needle is pulled out. At the same time, the needle will be withdrawn immediately, because inserting to the acupoints at a depth of 1.0 cm without retaining the needle to activate the *qi*, which is essentially different from traditional acupuncture.

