#### 2.7.3. Safety assessment

Adverse events that happen during the study will be recorded in the CRFs in detail, including the time of occurrence, symptoms, duration, treatment methods, and outcomes. Adverse events will be assessed by the specialists in the panel, to determine whether the conditions are treatment related and whether further rescues are needed. Adverse events frequently occurring in ACE treatment include fainting, acupoint swelling, and subcutaneous hemorrhage, and will be addressed by symptomatic treatment methods. Once the adverse events are defined as severe, such as acupoints infection, allograft rejection, or major organ damage, the research process will be terminated and the inspectors of the monitoring panel will reveal the participant’s allocated intervention at once. Consequently, the participant will withdraw from the study and accept systemic treatments. The cost of treatments for adverse events arising from this study will be paid by the sponsor of this study. The monitoring panel will report the SAEs to the ethics committee, while the researchers will closely follow the participants’ condition, and record it in detail in the CRF.

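### A shared arm letter in every CRF means that one disclosed allocation, or one recognised catgut-only reaction, could reveal to an assessor the arm of everyone assessed afterwards

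*Protocol article*

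**What the plan says.** Section 2.4 of the protocol article states an aim and a method. The aim is that "participants, outcome assessors, and statistician in the study will be blinded to the different treatments". The method given for the assessors is that they are blinded "due to the groups of the participants recorded in the case record forms (CRFs) being replaced by" the letters A and B. The section also says that assessors are kept unaware of recruitment and grouping, but gives no second mechanism for that.

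Three other places bear on the method:

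- **What else is in the form.** Section 2.8 has the outcome measures entered in the CRFs at six time points. Section 2.7.3 has adverse events entered there in detail. Table 2 schedules adverse events at the same visits as VAS, ODI, RMDQ and SF-36.
- **When an arm is disclosed.** Section 2.4 permits unblinding for serious adverse events and other emergencies. Section 2.7.3 goes further. Its rule opens "Once the adverse events are defined as severe, such as acupoints infection, allograft rejection, or major organ damage", and inspectors from the monitoring panel must then disclose that participant's arm without delay.
- **What follows.** Sections 2.3.4, 2.4 and 2.7.3 withdraw the unblinded participant. Nothing is said about the letters that the others carry.

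Section 2.6.2 states that the sham procedure leaves no catgut in the tissue.

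**The concern.** Saying that assessors are blind because a letter replaces the group name makes sense only if assessors see the letter. The letter identifies the arm, not the person. With two letters and two arms, learning what one participant received fixes the meaning of both letters. The plan itself provides for such disclosures during the trial.

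At stake is the claim in sections 2.1 and 3 that the trial is patient-assessor-blinded, which matters a great deal in a sham-controlled trial of a procedure. If an assessor learned the key part-way through, later administration of the scales would no longer be blind. The form would still show only A or B, so nothing in it would reveal the loss.

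**Working it through.** The plan gives no figure on this point, so there is none to reproduce. The check is one of logic, with an illustration under assumed rates.

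**Step 1: what one disclosure reveals.** Suppose that participant X has letter A and is found to have received catgut. Then A is ACE and B is sham. Anyone who knows this and sees the letters knows the arm of all 82 participants (41 + 41, section 2.1). With a participant-specific code only, the same disclosure reveals 1 of 82.

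**Step 2: how the link could become known.**

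1. *Disclosed allocation*, after a severe event (mandatory in section 2.7.3) or another emergency (permitted in section 2.4). This can happen in either arm. The text does not limit who is told.
2. *Recognised event.* Section 2.7.3 lists allograft rejection. Sham leaves no catgut (section 2.6.2), so a reaction to embedded material can occur only under ACE. The other examples are not specific: infection can follow needling in either arm. Nor are the common events (fainting, swelling, subcutaneous bleeding), because sham uses the same needle, points and depth.

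**Step 3: how often there might be an occasion.** The documents give no rate. For an assumed per-participant probability p and independent participants, P(at least one) = 1 − (1 − p)^n.

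| Assumed p | Catgut-specific event, n = 41 (ACE) | Disclosed allocation, n = 82 (both arms) |
|---|---|---|
| 1% | 1 − 0.99^41 = 0.338 | 1 − 0.99^82 = 0.561 |
| 2% | 1 − 0.98^41 = 0.563 | 1 − 0.98^82 = 0.809 |
| 5% | 1 − 0.95^41 = 0.878 | 1 − 0.95^82 = 0.985 |

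These are chances of an occasion for decoding, not of decoding. They must be multiplied by the probability that an assessor hears of the disclosure or recognises the event, and the documents give no basis for that figure.

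**Step 4: who is affected.** Assessments completed before the disclosure were made blind and stay so. The 82 in step 1 is therefore an upper limit. The number affected is those with visits still to come, and recruitment is spread from April 2022 to December 2024 (section 2.2).

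**The case against.** The strongest reply is that unmasking is conditional. The disclosure is made by a panel that section 2.9 describes as independent of the sponsor. Section 2.7 appoints assessors who have no other task in the study, and section 2.4 says that they are kept unaware of groupings. Nowhere does the text say that assessors are told a revealed arm. This stands, and it limits the point to what could happen. It does not remove the point: the letter is the only mechanism stated, events and outcomes share a form and a visit schedule, and nothing keeps a revealed arm from the assessors.

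A second reply also stands. Participants mark the VAS and answer the RMDQ themselves and are not said to see the letter. Bias through the assessor would therefore be indirect.

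Some stronger readings are tempting but not supported:

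- *The analyst is unmasked during the trial.* Section 2.8 has data extracted from the CRFs after completion and analysed only then.
- *The person who makes the sequence is the one declared blind.* Section 2.4 says "The random numbers of allocation sequences will be generated using Statistical Analysis System (version 9.4) by a statistician" but does not say that this is the analysing statistician. A condensed article may leave that open.
- *Blinding is never tested, or sham lacks the dressing and aftercare.* Silence on these points in an article is not evidence that they are absent.
- *The sham itself gives the arm away.* ACE operators "apply lifting, inserting, and twisting techniques to stimulate special sensations", whereas for sham the text says "At the same time, the needle will be withdrawn immediately". This is a real stated difference, but it concerns sham credibility and is a separate matter that recoding the CRF does not touch.

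**Conclusion.** The point holds in a limited form. The protocol rests assessor blinding on a label shared by a whole arm, on the form that also records outcomes and adverse events. It provides for individual disclosure during the trial and describes no recoding afterwards. One disclosure could therefore expose all remaining assessments, where a participant-specific code would expose one person.

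This assumes that assessors see the letter, which the stated reason for their blinding implies, and that at least one of them learns the revealed arm or recognises a catgut-only reaction. The 34%, 56% and 88% rest on assumed rates of 1%, 2% and 5% and show only how often an occasion might arise. A reader might infer that any severe event unmasks the whole trial. The documents do not support that, because the knowledge must reach an assessor and earlier assessments stay blind. The weakness does not invalidate the trial, but it is worth removing because the remedy costs so little.

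**What to change.** Make these changes:

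1. Remove the arm letter from the CRFs and identify participants only by the number-based identifier that section 2.8 already creates.
2. Leave the list linking number to arm with the researcher who keeps the marked envelopes (section 2.4) and who takes no part in recruitment. A single participant can still be unblinded in an emergency, and that disclosure then says nothing about anyone else.
3. Attach A/B codes to the dataset for the statistician only after database lock. The blinded analysis is preserved, and the letters never exist where assessors work.

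The cost is a small change to the CRF template and one merge by participant number at the end. No visits, staff or participants are added. Section 2.12 says that enrolment has begun, so forms already in use need their letters removed or covered. If the change is judged to affect conduct, it goes through the modification procedure in section 2.1.

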### 2.5. Sample size

The VAS score is the primary outcome indicator for this trial. Based on the results of the pre-test, it is known that the VAS score in the control group was 4.64 ± 1.42 cm and is expected to be reduced by 1.02 cm after treatment with ACE, setting a two-sided test with α = 0.05, β = 0.10. A sample size of 34 cases per group was calculated using PASS 15 software. Considering the 20% lost to follow-up calculation, the final number of cases needed for at least two groups was 41, for a total of at least 82 participants included.

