## 2. Methods

### 2.1. Design and setting

The present study will be a prospective, randomized, patient-assessor-blinded, sham-controlled trial. A total of 82 participants will be recruited for the trial in Guangzhou Panyu Hospital of Chinese Medicine. Participants will be divided randomly at a ratio of 1:1 into the ACE group or the sham ACE group. The trial will contain an enrolment and allocation period of 3 days, an 8-week intervention period, and a 6-month follow-up period. The flow chart of the study procedure is shown in Figure 1. This study will be conducted in accordance with the Declaration of Helsinki, the Consolidated Standards of Reporting Trials (CONSORT) (Schulz et al., 2010) and the Standards for Reporting Interventions in Controlled Trials of Acupuncture (STRICTA) guidelines (MacPherson et al., 2010) in trial design and reporting. Any modifications to the protocol that may affect the conduct of the study will be expected to draft a formal modification of the protocol. Such update will be determined by the project management group and approved by the ethics committee, before the modification being placed into practice. This trial has been registered at the Chinese Clinical Trial Registry, numbered ChiCTR2200059245.

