### 2.10. Statistical analysis

Statistical analysis will be computed using Statistical Analysis System (SAS) v9.4 by a statistician. Continuous variables subject to normal distribution are expressed as mean ± standard deviation, otherwise they will be expressed as median (interquartile range). Discontinuous variables will be expressed as composition ratio and rate. The baseline comparison of continuous variables will be performed by *t*-test or non-parametric test, and the baseline comparison of discontinuous variables by the chi-squared test. Repeated measures analysis of variance (RM-ANOVA) will be performed on the measurement data at multiple observation time points, to analyze the trend over time and the interaction between treatment times. The statistical significance level will be 0.05 (bilateral) with 95% confidence interval. The safety analysis will mainly be based on descriptive statistics, including the incidence and the specific description of adverse events.

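### The 34 per group does not follow from the stated two-sided inputs (42 are needed), and 41 randomised per group do not protect 34 against 20% loss, so the 90% power is not supported as printed

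*Protocol article*

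**What the plan says.** Section 2.5 names the VAS score as the primary outcome and takes its planning values from a pre-test: "the VAS score in the control group was 4.64 ± 1.42 cm", and this "is expected to be reduced by 1.02 cm after treatment with ACE". The error rates are given as "setting a two-sided test with α = 0.05, β = 0.10". The result is "A sample size of 34 cases per group was calculated using PASS 15 software", followed by "Considering the 20% lost to follow-up calculation, the final number of cases needed for at least two groups was 41". The overall minimum is then put at 82 participants. Section 2.1 fixes equal allocation. Section 2.10 also sets the significance level at 0.05 two-sided. No one-sided test appears anywhere in the article, and only one SD is given, that of the control group.

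Section 2.3.4 bears on how many participants are analysed. The last outcome values of dropouts are kept in the analysis, and withdrawals and dropouts enter the intention-to-treat analysis. Some enrolled participants are removed altogether, including those without evaluable records.

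**The concern.** There are two independent steps, and neither works as printed. First, a standardised difference of 1.02/1.42 = 0.718 at two-sided 5% and 90% power needs clearly more than 34 per group. Second, adding 20% to the required number is not the same as allowing for 20% of the randomised participants to be lost.

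The stakes are the claimed type II error of 0.10 for the primary outcome. If power is nearer 82%, the risk of missing a true 1.02 cm benefit is about 0.18 to 0.19. A reader who takes the 90% at face value would then give a null result more weight than it deserves.

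**Working it through.** **Inputs.** Difference δ = 1.02 cm; SD σ = 1.42 cm, taken as common to both arms because only one is given; two-sided α = 0.05; power 0.90; loss 20% (all Section 2.5); allocation 1:1 (Section 2.1). The comparison is of two independent means at one time point.

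**Step 1: can 34 be reproduced?** The normal approximation is n = 2 × [σ(z for α + z for power)/δ]². The t-test figures use the noncentral t distribution.

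| Test | Power | n per group, normal approximation | n per group, t-test |
|---|---|---|---|
| Two-sided 5% (as stated) | 90% | 40.7 → 41 | 42 |
| Two-sided 5% | 85% | 34.8 → 35 | 36 |
| Two-sided 5% | 80% | 30.4 → 31 | 32 |
| One-sided 5% | 90% | 33.2 → 34 | 34 |

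For the stated row: 2 × [1.42 × (1.960 + 1.282)/1.02]² = 40.7. The figure 34 is 8 below the t-test requirement, 8/42 = 19%, which is too much for rounding or for the choice between z and t.

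**Step 2: what would give 34?** The one-sided 5% row does so exactly (one-sided t-test power at 34 per group is 90.1%). So does a two-sided test with a smaller SD in the ACE arm. With an ACE SD of 1.11, the average SD is √[(1.42² + 1.11²)/2] = 1.274, and two-sided t-test power is 89.3% at 33 per group and 90.2% at 34. The printed inputs do not distinguish these two explanations.

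**Step 3: the loss allowance.**
- Printed route: 34 × 1.2 = 40.8 → 41.
- Evaluable after 20% loss: 41 × 0.8 = 32.8, below 34.
- Needed to protect 34: 34/0.8 = 42.5 → 43.
- Loss that 41 can tolerate: 1 − 34/41 = 17.1%.

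This shortfall does not depend on which SD was entered or on the sidedness of the test.

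**Step 4: two-sided power on the printed inputs (t-test, δ = 1.02, σ = 1.42).**

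| Analysed per group | Situation | Power |
|---|---|---|
| 32 | after 20% loss, rounded down | 80.7% |
| 33 | after 20% loss, rounded up | 82.0% |
| 34 | the article's target | 83.1% |
| 41 | everyone analysed, no dilution | 89.5% |

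At 33 per group the difference detectable with 90% power is about 1.15 cm, against the planned 1.02 cm.

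**Step 5: both steps done on the printed inputs.** 42/0.8 = 52.5 → 53 per group, 106 in total (by normal approximation 41/0.8 = 51.25 → 52 per group, 104 in total), against the planned 82.

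**The case against.** The best case for the plan has three parts.

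*The cause is not established.* A reader might infer that the software was run one-sided by mistake. The article does not support that as a fact: it says two-sided in both places, and the only evidence is a numerical match that an unreported ACE-arm SD of about 1.11 cm produces equally well. A condensed article may have dropped that second SD. This stands. What remains is that 34 cannot be reproduced from what is printed. Even with that SD, the loss step still falls short: power would be 88.3% at 32 and 89.3% at 33 per group.

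*The trial may analyse more than 33 per group.* A reader might infer that its power simply is 82%. That holds only if the 20% counted as lost are left out. Section 2.3.4 keeps dropouts' last values, and with all 41 analysed power would be 89.5%, close to the stated figure. This stands as an upper end. It needs the carried-forward values to show the full 1.02 cm effect, which cannot be assumed for people who left early. If the mean difference were diluted by 10%, to 0.918 cm, power at 41 per group would be about 82% again. Section 2.3.4 also removes some participants entirely, and Section 2.5 itself treats the 20% as lost. That 41 nearly equals the two-sided requirement before loss is a coincidence, since the article derives it from 34 plus 20%.

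*The loss formula is the smaller error.* This is true: 43 instead of 41 randomised raises the evaluable number from about 33 to 34, and power from 82.0% to 83.1%. Most of the gap comes from the 34.

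**Conclusion.** The point holds as a failure of the printed calculation. The stated inputs need 42 evaluable per group (41 by normal approximation), not 34, and 41 randomised per group do not deliver even 34 after 20% loss. On those inputs, two-sided power is 83.1% at the target of 34 and 80.7% to 82.0% after the planned loss, a type II error of about 0.18 to 0.19 against the stated 0.10. The upper end is 89.5%, if all 41 per group are analysed without dilution.

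These figures rest on three assumptions: a common SD of 1.42 cm, 1.02 cm read as the between-group difference, and a two-sample comparison at a single time point. Why 34 was obtained remains open. A one-sided run is possible but not shown.

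**What to change.** Keep 82 participants and rewrite the calculation in Section 2.5:

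- State 41 randomised per group, about 33 evaluable after 20% loss, and two-sided power of about 82% for a difference of 1.02 cm with SD 1.42 cm. If an ACE-arm SD was entered in the software, state it and recompute the power from it.
- Use n/(1 − 0.20) for the loss allowance, or state that 41 per group tolerates only 17% loss if 34 are to remain.
- Optionally, specify a baseline-adjusted analysis of the primary outcome. Section 2.10 does not plan one now; it names repeated measures analysis of variance. With residual SD 1.42 × √(1 − r²), 33 per group would reach about 90% power if the correlation r between baseline and outcome is about 0.47 or more. That correlation is an assumption, as the article gives none.

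The cost is one paragraph and a less favourable stated power. No further recruitment is required. The optional third item would also need a change to the analysis section.
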